**Figure 1 F1:**
[figure not shown]
Economic evaluation logic model (data are not available for the purple-coloured inputs).

However, it may not be possible to assess all potential resources and consequences in this economic evaluation, illustrated in an economic evaluation logic model. In light of our available data and sources assessment, we report in table 1 the resource uses/costs and consequences that might be amenable to assessment in our analysis from the logic model.

**Table 1 T1:** Resources and outcomes with data sources that will be captured in the economic evaluation

Resource uses and outcomes	Data captured?	Data sources
**Resource uses/inputs**		
** *Administrative and implementation costs for applying and enforcing later trading hours* **		
Cost to obtain permission to administer later trading hours	Yes	Data from the qualitative studies and secondary published sources will be used.
Cost to operate later trading hours (eg, staff’s salary, venue maintenance cost and others)	Yes	Data from the qualitative studies and secondary published sources will be used.
**Outcomes/consequences**		
** *Negative consequences* **		
Alcohol-related ambulance call-outs (primary consequences)	Yes	Scottish Ambulance Service (time series data)
Total ambulance call-outs (secondary outcomes)	Yes	Scottish Ambulance Service (time series data)
Reported crimes (secondary outcomes)	Yes	Police Scotland (time series data)
Alcohol-related road traffic accident	No	Design not amenable to data capture.
Reduced workforce participation due to sickness	No	Design not amenable to data capture.
Reduced household labour due to sickness	No	Design not amenable to data capture.
Reduced workforce and household labour due to premature mortality	No	Design not amenable to data capture.
Increased burden to the social service sectors	Yes	Data from the qualitative studies and secondary published sources will be used.
Increased additional consumer’s spending during later or expanded premises hours	No	Design not amenable to data capture
** *Positive consequences* **		
Increased profit (retailer) due to later trading hours	No	
Increased pleasure (consumer) due to additional time for social interaction	No	

### Comparators

This study examines the impact of policy changes on outcomes and costs that are sensitive to both observed and unobserved confounding effects, due to the non-randomised study design. Therefore, based on the analysis of effectiveness, we will implement a control ITS study design (if we find a suitable control group). Economic evaluation methods also need to adapt to the challenges associated with non-randomisation and select an appropriate control group that closely approximates the intervention cities (Glasgow and Aberdeen). The objective of the control in an ITS study is to minimise biases caused by time-varying confounders, seasonality or other events that occurred during the implementation of policy changes.^52^ In this study, we will use a location-based control if we can identify any appropriate candidates. In a location-based control, different geographical areas with similar features, where the policy or intervention has not been adopted, are typically chosen. The process of suitable control selection and corresponding study design has been outlined in the flow diagram (figure 2).

**Figure 2 F2:**
[figure not shown]
Flow diagram for the control selection procedure.

In this study, we will assess the appropriateness of the 30 Scottish councils/cities (except intervention cities—Aberdeen and Glasgow) as potential controls. No policy changes that were comparable to those in Aberdeen and Glasgow took place during our initial assessment. Later trading hours were temporarily changed for holidays (eg, Christmas and New Year), but we expect that intervention cities were similarly impacted. The appropriateness of the potential control candidates will be tested by visually and statistically assessing the assumption of parallel trends.^59^ Graphically, we will observe the preintervention differences between the intervention and control groups. If the parallel test assumption holds, then the preintervention differences will be constant over time. There are no formal statistical tests for this assumption, and passing the parallel test does not necessarily mean that the parallel trend is true.^59^ However, failing the parallel tests will make the parallel trends assumption less plausible.

If none of the potential control candidates satisfy the parallel trends assumption, we will proceed with an uncontrolled ITS study design (figure 2). In addition, we will construct a synthetic control based on all potential control candidates since synthetic control does not need to satisfy parallel trends and will proceed with a controlled ITS study design.^60^ The synthetic control method (SCM) is widely recommended for ITS designs where multiple prospective control groups are available.^52 61^ The SCM is a data-driven process that builds a control series by calculating a weighted average of potential controls.^61^ To generate weights for the SCM, we will collect data from all Scottish councils/cities in addition to Glasgow and Aberdeen. The weights will be generated based on pre-intervention outcomes of potential control groups so that the preintervention trend of synthetic control matches well with the intervention. This process will be followed twice to generate synthetic controls for Aberdeen and Glasgow. Along with preintervention outcomes, other covariates representing time-varying confounding such as per capita gross disposable household income,^62^ number of alcohol premises/population-adjusted alcohol premises^63^ and weather (mean temperature and rainfall from the Centre for Environmental Data Analysis archive) will be used to generate weights for the synthetic control. In order to determine more accurate weights for the synthetic control series, we will incorporate population size-adjusted alcohol-related ambulance call-out and reported crimes rates for all regions in Scotland. We anticipate that, by using population-adjusted rates, the SCM series will yield a closer match to the observed outcomes prior to the intervention.

If at least one candidate satisfies the parallel trends assumption, we will assess the qualitative and quantitative evidence on control group suitability. For example, we will qualitatively assess whether other policy changes similar to later hours occurred at the selected control cities after our initial assessment through reviewing published reports, which might limit their suitability. In addition, we will consider on-premises outlet density per 1000 population, socioeconomic and geographical features to match with the intervention context. If potential controls only satisfy the parallel trends assumption but did not get support from the qualitative and quantitative assessment, we will proceed with an uncontrolled ITS study design. However, if only one candidate satisfies both parallel trends assumption and is supported by further evidence, we will proceed with a controlled ITS study design. We will calculate mean squared prediction errors (MSPEs) for each of them, if more than one candidate satisfies both the parallel trends assumption and has favourable qualitative and quantitative evidence support. If we get only one smallest MSPE with a clear differential to other values, we will use that corresponding control and proceed with a controlled ITS study design. In addition, we will construct a synthetic control based on the selected control groups and will proceed with a controlled ITS study design based on the synthetic control. However, if there are more than one similar smallest MSPEs (ie, two or more very close MSPEs), we will select the most suitable control qualitatively and will proceed with a controlled ITS study design based on the corresponding control. We will also construct synthetic control by incorporating selected control candidates and proceed only with a controlled ITS study design.

We will assess whether any such preintervention and postintervention changes are likely to be caused by the intervention, by analysing the data for the suitable control (if any). We will use a difference-in-difference approach, such that differences between intervention and control will be used as outcome variables for both primary and secondary outcomes.

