#### Consequences

The economic evaluation will incorporate a number of multisectoral consequences (which can also be thought of as costs/cost savings), including not only to the health service but also the judicial system. The outcomes (consequences) of this study were chosen based on the common alcohol-related harms and outcomes considered in the earlier literature to measure the impact of later trading hours. The primary outcome (consequence) will be alcohol-related ambulance call-outs (table 1). We will collect time series data from the Scottish Ambulance Service for recorded ambulance call-outs in Scotland. The available recorded electronic data on ambulance call-outs include the number of call-outs with date and time, age group, gender and council name. Using a previously developed algorithm, we will then determine which recorded ambulance call-outs are alcohol-related.^31^ To precisely evaluate the effect of the two policies regarding later trading hours for bars and clubs in Glasgow and Aberdeen, we will analyse alcohol-related ambulance call-outs that occurred throughout the weekend night-time (ie, from Friday, 20.00 to Saturday, 6.00 and Saturday 20.00 to Sunday 6.00). In addition, we will analyse all weekend night-time ambulance call-outs and reported crimes as secondary consequences (table 1). Anonymised individual data on reported crimes will be obtained from the Police Scotland IT system. We will use the Scottish Government Justice Directorate crime codes to identify crimes likely linked to alcohol consumption. This dataset will contain types of crimes with date and time, location, etc. Due to a lack of available data, we are not able to measure costs for alcohol-related road-traffic accidents, productivity losses due to alcohol-related harms (ie, reduced workforce participation due to sickness, reduced household labour due to sickness, reduced workforce and household labour due to premature mortality), increased profit for retailers due to later trading hours and increased pleasure for consumers due to additional time for social interaction.

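### Councils bordering Aberdeen and Glasgow stay eligible as controls, and no stated selection step tests for spillover that begins with the policy

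*Protocol article*

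**What the plan says.** The Comparators section defines the candidates: "we will assess the appropriateness of the 30 Scottish councils/cities", with only Aberdeen and Glasgow left out. For the synthetic-control weights, "we will collect data from all Scottish councils/cities in addition to Glasgow and Aberdeen".

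Selection then depends on whether any candidate shows parallel trends with the intervention city before the policy.

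- **None does.** An uncontrolled interrupted time series is run, and in addition "we will construct a synthetic control based on all potential control candidates since synthetic control does not need to satisfy parallel trends". No further screen of the donors is described in this branch.
- **At least one does.** The candidate is checked for later-hours policies of its own, and "we will consider on-premises outlet density per 1000 population, socioeconomic and geographical features to match with the intervention context". Survivors are ranked on mean squared prediction error (MSPE), and any synthetic control uses the selected candidates only.

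On weighting: "The weights will be generated based on pre-intervention outcomes of potential control groups", together with income, number of alcohol premises and weather. The section ends by making the difference between intervention and control the outcome variable for primary and secondary outcomes.

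Two other places bear on the point. Study design bases the value of controls on their not having been exposed to the intervention. Setting and location draws the controls from other cities in Scotland without such a policy, which is narrower than the 30 councils in Comparators.

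**The concern.** A council can be free of the policy and still be affected by it. If city venues stay open later, people from a neighbouring council may go to the city or stay there longer, so that call-outs at home fall. They may also return later and more intoxicated, so that call-outs at home rise. In either case the neighbour no longer shows what would have happened without the policy, which is the standard the article sets in Study design.

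The steps that decide who becomes a control would not reveal this. A pre-policy comparison carries no information about a change that begins with the policy. Looking for similar licensing changes in the control concerns the control's own rules, not where its residents drink. Matching on geography rewards similarity and does not exclude on proximity.

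The effect on the primary outcome feeds the economic results. Under Analysis of costs and consequences, the number of extra or avoided call-outs is multiplied by unit cost, so an error in that number passes in proportion into that part of the incremental cost.

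**Working it through.** **1. Is there a rule that would remove a bordering council?** The article gives no figure to reproduce here, so each selection step is read for what it can detect.

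| Step (Comparators) | What it examines | Detects spillover that begins with the policy? |
|---|---|---|
| Candidate list | All councils except the two cities | No |
| Parallel trends | Differences before the policy | No |
| Suitability: similar policies | The candidate's own licensing changes | No |
| Suitability: outlet density, socioeconomic and geographical features | Similarity to the city | Not by its wording; judgement could drop a neighbour |
| MSPE | Closeness of fit (the window is not stated; taken here as pre-policy, the usual use) | No |
| Synthetic-control weights | Pre-policy outcomes and covariates | No |

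Reporting and discussion lists non-randomisation and data quality among the limitations, but not displacement or spillover.

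**2. How would spillover enter the estimate?** Set both series to an index of 100 before the policy. Let

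- e = true change in the city,
- w = weight on affected bordering councils in the control (1 if one of them is the single control),
- s = policy-induced change in those councils, with no such change in the other controls.

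Estimate = e - w x s, so bias = -w x s.

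**3. Illustration.** The article gives none of e, w or s. The values below are assumptions, and the entries are bias in index points.

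| w | s = -5 | s = -2 | s = +2 | s = +5 |
|---|---|---|---|---|
| 0.25 | +1.25 | +0.5 | -0.5 | -1.25 |
| 0.5 | +2.5 | +1.0 | -1.0 | -2.5 |
| 1.0 | +5.0 | +2.0 | -2.0 | -5.0 |

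- With e = 0, w = 0.5 and s = -5, the estimate is 0 - (0.5 x -5) = +2.5: an apparent harm where there is none.
- With e = 5, w = 0.25 and s = -2 or +2, the estimate is 5.5 or 4.5, an error of 0.5/5 = 10%.
- With e = 5, w = 1 and s = -5 or +5, the estimate is 10 or 0. This is an extreme case: the neighbours move as much as the city does.

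The bias is linear in s, so half the spillover gives half the bias, and w = 0 or s = 0 gives none.

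**4. Exposure.** The policy section gives 10 of 1350 outlets in Glasgow (10/1350 = 0.7%) and about 38 of 430 in Aberdeen (38/430 = 8.8%). These are shares of outlets and do not measure cross-boundary travel.

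**5. Sign.** The call-out data carry "age group, gender and council name". The article does not say whether that is the council of the incident or of residence. A neighbour's resident injured in the city would count towards the city in the first case and towards the neighbour in the second, so the sign of s cannot be settled from the text.

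**The case against.** The strongest reply is that the 30 councils are candidates, not the control group. A neighbour does harm only if it is selected or weighted, and nothing in the article shows that it will be. This is right, and the point is worded conditionally for that reason.

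The suitability check is introduced by an example, so its list is not exhaustive, and a sensible team could use it to reject a neighbour. That also stands for the branch in which some candidate passes parallel trends. It does not help in the other branch, where the synthetic control takes all candidates with no screen described. There the uncontrolled analysis is run as well, and contaminated controls cannot affect it, but it also gives up the protection that a control provides.

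Control selection is also described in a separate statistical analysis plan, and the flow diagram is not visible here. Either may hold an exclusion rule. The article, however, does more than leave the matter open: it states the pool and the order of selection, and that stated pool removes only the two cities.

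A reader might infer that the selection rules steer towards neighbours because these share events or ambulance coverage with the city. The article does not support this. It mentions neither, and its criteria of income, premises and outlet density could equally favour more distant urban areas.

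A reader might also infer that Glasgow is at greatest risk because so few of its outlets were exposed and its true effect is probably small. That does not follow: the relative bias is w x s / e, and low exposure plausibly shrinks s along with e.

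**Conclusion.** The point holds as a conditional weakness in a stated rule. As written, the procedure can give weight to bordering councils that are plausibly exposed indirectly, contrary to the article's own requirement for controls, and none of its named tests is aimed at this. It is clearest in the all-candidates synthetic-control branch.

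It would go too far to say that displaced drinking will be read as a policy effect, or that the estimate will be wrong by some percentage. The formula bias = -w x s rests on the intervention-minus-control estimator. The numbers put into it are assumptions, and the article reports no cross-boundary flows. The bias could inflate or mask harm, and it may be small, particularly in Glasgow. The change is worth making before the analysis because it needs little work. The point does not invalidate the design.

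**What to change.** - In Comparators, for each city separately, exclude councils that share a boundary with it from the single-control candidates and from the synthetic-control donor pool, before trends or MSPE are assessed.
- Report the all-council pool as a sensitivity analysis. If the authors prefer to keep that pool as the main analysis, the minimum is the reverse: repeat the analysis without the bordering councils.
- Present the bordering councils as their own before-and-after series, so that readers can see whether call-outs or crimes moved across the boundary.
- Reconcile Setting and location (other cities) with Comparators (30 councils). If the separate statistical analysis plan already has an exclusion rule, state it in both documents.

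Data from all Scottish councils are already being collected, so this needs a change of wording and some additional model runs. The price is a smaller donor pool and possibly a slightly worse pre-period fit. Sharing a boundary is also only a rough marker of spillover, which is why both pools should be reported.

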### Setting and location

In this natural experiment, the selection of target population and study location is constrained by the location of policy changes/implementation.^48^ This study includes two Scottish cities as intervention sites (*the estimated effect will be at city level*), where 10 licensed alcohol premises in Glasgow and 38 licensed alcohol premises in Aberdeen were permitted to operate with later trading hours. So, our study target population will be those residents in these cities. The outcomes in these intervention cities will be compared with concurrent control areas to assess the impact of later trading hours. Control areas will be selected from other Scottish cities where such policies are not in place. Additionally, we will generate a synthetic control for both Aberdeen and Glasgow. The control selection procedure and synthetic control methodology are described below. To develop a controlled before-and-after evaluation, we will consider the dates from which the later closing time was permitted to be used by premises.

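### One branch of the control selection ends in an uncontrolled ITS with no synthetic control, and another names none, although the protocol promises one for both cities

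*Protocol article*

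**What the plan says.** The Setting and location section of the protocol article makes a general commitment: "Additionally, we will generate a synthetic control for both Aberdeen and Glasgow". It refers the reader to later text for the procedure, which is in the Comparators section around Figure 2.

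There the candidate pool is defined: "we will assess the appropriateness of the 30 Scottish councils/cities (except intervention cities", that is, all other councils. The first decision is whether any candidate meets parallel trends. If not, two analyses follow: "If none of the potential control candidates satisfy the parallel trends assumption, we will proceed with an uncontrolled ITS study design", and then "In addition, we will construct a synthetic control based on all potential control candidates since synthetic control does not need to satisfy parallel trends".

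If at least one candidate meets parallel trends, suitability is reviewed (similar policy changes, outlet density, socioeconomic and geographical features). Candidates that meet parallel trends but fail this review lead to the sentence ending "did not get support from the qualitative and quantitative assessment, we will proceed with an uncontrolled ITS study design". The next rule is: "if only one candidate satisfies both parallel trends assumption and is supported by further evidence, we will proceed with a controlled ITS study design". Neither rule mentions a synthetic control. Where several candidates qualify, a single control is chosen by mean squared prediction error (MSPE), or qualitatively if the errors are close, and a synthetic control is added in both cases.

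The section Analysis of costs and consequences then applies unit costs to the number of extra or avoided events in each city.

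**The concern.** The justification given for building a synthetic control when every candidate fails parallel trends is that the method does not require that assumption. The same justification applies when some candidates pass but are judged unsuitable, because the remaining councils can still serve as donors. The rules nevertheless stop at an uncontrolled series in that case. A city could therefore receive a controlled estimate when no candidate passes the trend check and lose it when some do.

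At stake is protection of the costed effect from events common to Scotland. Comparators gives this as the reason for having a control, and Reporting and discussion names the synthetic control among the ways non-randomisation will be handled. Data run from 2015 to 2022 (Time horizon), a window that includes the pandemic closure of venues described in the account of the policy changes.

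A second, smaller matter is that several branches produce two effect estimates, while the economic analysis needs one count per outcome and city.

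**Working it through.** The plan has no figure to reproduce here. The check is an enumeration of the branches in Comparators, set against the commitment in Setting and location. The letters are mine.

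| Branch | Condition | Analyses named | Estimates | Synthetic control? |
|---|---|---|---|---|
| A | No candidate meets parallel trends | Uncontrolled ITS; ITS with synthetic control from all candidates | 2 | Yes |
| B | Parallel trends met, suitability not supported | Uncontrolled ITS | 1 | Not named |
| C | Exactly one candidate meets both | ITS with that control | 1 | Not named |
| D | Several meet both, one clearly smallest MSPE | ITS with that control; ITS with synthetic control from selected candidates | 2 | Yes |
| E | Several meet both, MSPEs close | ITS with a qualitatively chosen control; ITS with synthetic control from selected candidates | 2 | Yes |

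**Count.** A synthetic control is named in 3 of 5 branches (A, D, E) and absent from 2 (B, C). Branch B alone has no control of any kind. Two estimates arise in 3 of 5 branches (A, D, E).

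**Why B and C may have come out this way.** In D and E the donors are the selected candidates. Under that rule B has no donors, and C has one, so a weighted average would simply reproduce that council. But A also has no selected candidates, and there the plan turns to the full pool. Nothing in the text explains why B and C cannot do likewise. Comparators already plans data from all councils to generate the weights.

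**What branch B exposes.** Let e be the true proportional policy effect and s a proportional change common to all Scottish councils that coincides with the policy and is not modelled.

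- Uncontrolled: apparent effect = (1 + e)(1 + s) − 1.
- With a control that fits well before the intervention and shares s: apparent effect = (1 + e)(1 + s)/(1 + s) − 1 = e.

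With e = 0 and an assumed s = −0.10, the uncontrolled result is 1 × 0.90 − 1 = −10%, and the controlled result is 0.90/0.90 − 1 = 0. When e = 0 the uncontrolled bias equals s for any s, so over an assumed range of s from −10% to +10% it runs from −10% to +10%. The documents give no value for s.

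**Which estimate is costed.** Perspectives uses the term base case for the NHS viewpoint, not for an effect estimate. Uncertainty and sensitivity analysis lists cost components and viewpoints, not the choice of control. Within the article, no sentence ranks the two estimates in A, D or E.

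**The case against.** The best defence is that branch B merely omits a sentence. Its wording matches the opening of branch A ("If none of the potential control candidates satisfy the parallel trends assumption, we will proceed with an uncontrolled ITS study design"), where a synthetic control is then added. Together with the general commitment in Setting and location, this could mean that one is intended throughout. That is plausible, and it is why the point asks for reconciliation and does not assert that the method was deliberately dropped. Read literally, though, B and the commitment conflict.

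On the second matter, Study design says control selection is also described in a published statistical analysis plan, and Figure 2 is not shown. Either may name the costed estimate. The connecting words also hint that the first-named design leads, though in branch A that would put the uncontrolled series first. This part is therefore conditional.

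A reader might infer several stronger things that the documents do not support:

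- That better donors lead to a weaker design. The candidates in B have been judged unsuitable, so they are not better donors. The valid point is that other councils remain.
- That the branch can be picked after seeing the effect. The trend check and the synthetic weights use pre-intervention data, and the suitability review uses published reports and area features. The remark that "There are no formal statistical tests for this assumption, and passing the parallel test does not necessarily mean that the parallel trend is true" is the authors' own caveat.
- That neighbouring councils contaminate the pool through spillover. The article does not say which councils border either city or where their residents go out, and call-outs carry a council name that may reflect where the incident occurred. No border exclusion is asked for.
- That the synthetic control must be the base case in every branch. That is a debatable preference, and it would be unwise where the pre-intervention fit is poor.

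**Conclusion.** The inconsistency holds: 2 of 5 branches name no synthetic control against an unconditional promise for both cities, and one of the two has no control at all. If branch B is reached and followed as written, any unmodelled common change coinciding with the policy enters the costed effect in full. The 10% example is an assumption and shows the mechanism, not an expected bias. The protection from a synthetic control also assumes that it fits well before the intervention. Branch C is less serious because it still has a concurrent control.

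That 3 of 5 branches give two estimates is correct on the text. Whether the costed one is left open depends on the unseen analysis plan and Figure 2, so this is a request to confirm. The point deserves a change because the change removes a possible bias at almost no cost; it does not show the overall design to be unsound.

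**What to change.** Reword the branch rules in Comparators, and Figure 2 if needed, so that a synthetic-control ITS is run in every branch. In the two branches that now name none, draw donors from the wider set of councils and drop only those judged unsuitable for a stated reason, such as a similar policy change. Where exactly one candidate qualifies, the pool must extend beyond that council, or the synthetic control merely copies it.

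Unless the statistical analysis plan already does so, state before the effect is estimated which estimate feeds the base-case costs, subject to adequate pre-intervention fit, and report the other as a sensitivity analysis.

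The cost is a few sentences, possibly a redrawn figure, and a little more analysis. No new data are needed, since all-council series are already planned.
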